**Fig. 1 Fig1:**
[figure not shown]
Hearts and Parks Study Diagram

### Population

#### Study population

The intervention catchment area includes a 20-mile radius from the Edison Johnson Recreation Center. The majority of this radius is in Durham County, NC. The population is diverse: 42.2% non-Hispanic White, 38.6% African American, and 13.4% Hispanic. Approximately 62% of the population is below 185% of the federal poverty line. 66.2% of students in the Durham public schools over the 2016–2017 school year qualified for free and reduced lunch [40]. Patients referred to Healthy Lifestyles are representative of this population; administrative records estimate that between 65 and 82% of patients are enrolled in State Children’s Health Insurance Program or Medicaid.

#### Study recruitment and enrollment

Based on Healthy Lifestyles visit data (800 new patients/year) and pilot study data (100 subjects 5–12 years of age recruited in 9 months), we estimate that we can conservatively screen 500 subjects and enroll 270 in a 2-year enrollment period. We continuously monitor recruitment to ensure equal distribution among age groups, and plan to apply a stratification scheme if groups become imbalanced. As of April 2020, we have enrolled 261 children, with recruitment continuing through June 2020.

Primary care providers will refer eligible subjects using a novel Best Practice Alert (BPA, Epic) automatically generated by pre-specified inclusion criteria, and confirmed by a trained research assistant (Table 1). The BPA “fires” during the patient’s annual visit, and the pediatrician can click “ok to contact” or “opt out,” and this response enters a call list for the research staff to schedule the study visit. If the patient agrees to attend the study visit, the research coordinators complete the consent process with parents and assent with children, as approved by the Duke Health Institutional Review Board.

**Table 1 Tab1:** Inclusion, Exclusion, and Opt-out Criteria

Inclusion Criteria	
• Child age 5–18 years • Child body mass index ≥95th percentile • Parent can speak and read in English or Spanish • Parent ownership of a device that is able to receive and send text messages	
Exclusion Criteria	
• Live farther than a 20-mile radius from the Bull City Fit program site • Endogenous or genetic cause of obesity • Taking a medication that causes weight gain • Participation in a pediatric weight management program within 12 months • Parent or child significant health problem that would limit participation • Pregnancy in patients of child-bearing age	
Opt-out Criteria	
✓ Primary care physician opts patient out of study for reasons including: severe obesity (BMI > 160% of sex- and age-specific 95th percentile), urgent co-morbidities, parental unwillingness to be contacted by a research assistant, or at physician clinical judgment.	

#### Randomization

Patients who consent for participation will undergo randomization in a 1:1 ratio following the baseline visit. Randomization occurs using the Research Electronic Data Capture (REDCap) system. Research coordinators notify patients of their assigned group following the baseline visit. Given the nature of the intervention, it is not possible to blind patients or providers to treatment assignment; therefore, unblinded randomization will be conducted.

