### Measurement strategy

#### Trial measures

##### Body mass index:

The primary study outcome is BMI obtained through standardized measures of body weight and height using a digital scale and stadiometer [43]. Measures will be obtained at all data points. A large number of children referred to the healthy lifestyles clinic have a BMI significantly greater than the 95th percentile, and known challenges exist in measuring changes in BMI at extreme values. Therefore, as recommended by Flegal et al. we will assess and report child relative BMI, expressed as a standard deviation score (zBMI) and as a percent of the BMI value at the 95th percentile (%95th BMI) to evaluate and track obesity [44].

Cardiorespiratory Fitness is the principal secondary outcome, and will be assessed by heart rate at the completion of the YMCA submaximal bench-stepping test [45]. This was chosen over others due to its sensitivity to fitness-related changes in heart rate and ease of implementation in a mobile setting.

Given the complexity of pediatric obesity, a variety of secondary outcomes, including cardiovascular measures, social and emotional health, and behaviors, will also be assessed. Blood pressure will be measured with a calibrated auscultatory sphygmomanometer in the seated position with an appropriately sized cuff using standard methods [46]. Fasting blood sample for cardiometabolic biomarkers, including lipids, glucose, and transaminases will be obtained. Body fat percent will be measured using calibrated bioelectrical impedance. Parent BMI will be directly measured from parent height and weight using calibrated stadiometers.

Weight-specific quality of life will be measured using the validated “Sizing Me Up” child obesity-specific instrument, which has been used previously in the Healthy Lifestyles clinic population [47]. Research staff will administer survey-based instruments to the parent, child, or both to assess child temperament, mood, peer relationships, perceived family support, and body-esteem. We will employ measures developed by NIH PROMIS®, a patient-reported outcomes data management system to encourage more universal measurement of clinical outcomes across studies [48]. PROMIS is a data management system that allows researchers to choose independently validated items from domain-relevant item banks.

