### Trial study procedures

#### Data collection strategy

At the beginning of the intervention, all consented subjects (*n* = 270) have a baseline visit with a trained research assistant to collect clinical data, perform fitness testing and laboratory testing. Subjects are given an activity tracker to wear for the duration of the study. For those randomized into the intervention group, all measures for the study will be collected at routinely scheduled visits to the Healthy Lifestyles clinic at 3 months, 6 months, 9 months, and 12 months. Control subjects will have a study-only visit at baseline and at 3 months. At 6 months, control subjects will be crossed over to the intervention, and we will obtain measures at routinely scheduled Healthy Lifestyles clinic visits at 6 months, 9 months, and 12 months, which will correlate to intervention time points of baseline, 3 months, and 6 months. Clinical data are managed via REDCap, which provides a secure method of managing data to protect patient confidentiality. Surveys are completed directly in REDCap; additional are collected during study visits and as part of routine clinical care. Data are reviewed regularly for completeness. For biospecimens, participants are given a stool sample requisition kit, and either provide sample at the time of enrollment or produce sample at home. Samples are frozen immediately in a − 30 degrees (F) freezer (home or clinic), transported on dry ice, and then stored permanently at − 80 degrees (F). Serum samples for metabolomics are collected in the fasting state and immediately processed on site, and transported to the Duke Molecular Physiology Institute for further processing and storage.

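### Unblindable families and providers do not justify unmasked outcome measurement: visit type differs by arm at 3 months, and at 6 months the visit can reveal the arm to whoever takes blood pressure and runs the step test

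*Protocol article*

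**What the plan says.** On blinding, the Randomization section states that "it is not possible to blind patients or providers to treatment assignment; therefore, unblinded randomization will be conducted". It adds that "Research coordinators notify patients of their assigned group following the baseline visit".

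On who measures and where, the Data collection strategy section differs by time point and by arm:

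- Baseline, everyone: subjects "have a baseline visit with a trained research assistant to collect clinical data, perform fitness testing and laboratory testing".
- Follow-up at 3, 6, 9 and 12 months, intervention arm: "For those randomized into the intervention group, all measures for the study will be collected at routinely scheduled visits to the Healthy Lifestyles clinic". The Intervention section makes the visits to this clinic at baseline, 3 and 6 months part of the treatment.
- Controls, first half: "Control subjects will have a study-only visit at baseline and at 3 months".
- Controls from the crossover: "we will obtain measures at routinely scheduled Healthy Lifestyles clinic visits at 6 months, 9 months, and 12 months". The 6-month visit serves as their baseline for the delayed intervention.

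On what is measured, the Methods/design section places fitness-test heart rate under hypothesis 2a, and blood pressure and lipids under 2b. In the trial measures section, "Blood pressure will be measured with a calibrated auscultatory sphygmomanometer", with the child seated; Table 2 gives the position as supine.

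**The concern.** The word 'therefore' in the Randomization section carries more than its premise allows. A family cannot be kept unaware of twice-weekly community sessions, nor can the clinicians treating the child. The person holding the stethoscope or running the step test is neither, and that person's knowledge of the arm is a separate choice. The article concludes that the trial is open and then describes a measurement plan tied to treatment visits, with no masking of measurement.

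Two things are at stake. At 3 months, a difference between arms could reflect the kind of visit rather than the programme. At 6 months, the principal secondary outcome (step-test heart rate) and the blood pressure part of hypothesis 2b could be affected by a measurer who knows which child has just completed the programme.

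**Working it through.** No stated figure has to be reproduced. The check sets the schedule in Table 2 against the visit plan in Data collection strategy.

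**Step 1: visit type by arm**

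| Visit | Intervention arm | Control arm | Differs by arm? |
|---|---|---|---|
| Baseline | Research assistant, before the arm is disclosed | Same | No |
| 3 months | Treatment-clinic visit | Study-only visit | Yes |
| 6 months | Treatment-clinic visit, end of treatment | Same clinic, entry to treatment | Same place; the visit can reveal the arm |
| 9 and 12 months | Same clinic, after treatment | Same clinic, during and at the end of the delayed treatment | Same place |

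**Step 2: which outcomes fall where (Table 2)**

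- BMI, body fat and waist are taken at all five visits, so they are the clinic measures exposed to the 3-month difference in visit type.
- Blood pressure, step test and lipids are taken at 0, 6 and 12 months only. The 3-month difference in visit type does not reach any Aim 2 outcome.
- At 6 months, auscultatory blood pressure is read by a person. The step test is administered by a person, and how heart rate is read is not stated. Lipids are laboratory values. BMI comes from a digital scale and a stadiometer, so only the height reading leaves some room for the observer.

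**Step 3: size of a height offset (illustration)**

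BMI is weight divided by height squared, so reading height h as h + 0.5 cm lowers BMI by the fraction 1 − (h/(h + 0.5))².

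- h = 130 cm: 1 − (130/130.5)² = 0.76%
- h = 150 cm: 1 − (150/150.5)² = 0.66%
- h = 165 cm: 1 − (165/165.5)² = 0.60%

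At an assumed BMI of 30 kg/m², these are 0.23, 0.20 and 0.18 kg/m². The 0.5 cm offset, the heights and the BMI of 30 are assumptions. The article has no reference values for converting the result to zBMI.

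**Step 4: what an arm-dependent shift does to the error rate (illustration)**

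Inputs from the Sample size section: 270 subjects, 30% lost before 6 months, two-sided alpha 0.05. With 1:1 allocation, 135 × 0.70 = 94.5 per arm; applying this retention to blood pressure and heart rate is an assumption. For a measurement shift of b standard deviations between arms and no true effect, the normal approximation for two independent groups gives

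false-positive rate = Φ(b/√(2/n) − 1.96) + Φ(−b/√(2/n) − 1.96).

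With n = 94.5, √(2/n) = 0.1455. For b = 0.10, b/0.1455 = 0.687, and Φ(−1.273) + Φ(−2.647) = 0.102 + 0.004 = 10.6%.

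| Assumed shift (SD) | False-positive rate |
|---|---|
| 0 | 5% |
| 0.05 | 6.4% |
| 0.10 | 10.6% |
| 0.20 | 28% |
| 0.30 | 54% |

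The article gives no basis for choosing a row. The table shows only how sensitive a comparison of this size is to a shift.

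**The case against.** The strongest reply is that this is a condensed article of a pragmatic trial. Measuring at routine visits is deliberate, the article never says that measurers know the arm, and a fuller protocol may provide for masking. Part of this stands: silence on staffing is no finding. But the article draws an explicit conclusion from an incomplete premise and sets out an explicit visit plan that differs by arm at 3 months. Both can be judged as written.

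A reader might infer several stronger things, which the text does not support:

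- **That Aim 2 outcomes are measured in different settings by arm.** They are not taken at 3 months, and from 6 months both arms attend the same clinic.
- **That different staff measure the two arms, or that the coordinator who tells a family its allocation also measures the child.** The article names a research assistant at baseline and trained personnel for waist. It does not say who takes the other follow-up measures.
- **That bias would favour the programme.** No direction is given. If encouragement raised effort in a submaximal test, heart rate would rise, which reads as worse fitness.
- **That the primary result is compromised.** The 6-month BMI is instrument-based and taken in the same place in both arms. How far 3-month values influence the 6-month estimate depends on how the repeated-measures model treats time; the article says only that repeated observations are accounted for.

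It is also fair to object that changing procedure now would mix methods within the trial, since 261 of 270 children were enrolled by April 2020. That is a real cost and belongs in the fix.

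**Conclusion.** The point holds in a limited form. The Randomization section does not justify unmasked outcome measurement. At 3 months, visit type is confounded with arm for BMI, body fat and waist. At 6 months the place is the same, but the nature of the visit can reveal the arm to whoever reads blood pressure and runs the step test. Lipids are not exposed to observer reading, and the 6-month BMI primary outcome is at most weakly exposed.

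This shows that bias is possible, not that it occurs. Its direction and size cannot be learned from the article, and the two illustrations rest on assumed shifts. The conclusion also assumes that the full protocol does not already provide for masked measurement. On that footing it is a worthwhile, inexpensive improvement rather than a threat to the main result.

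**What to change.** In Randomization and Data collection strategy, keep families and providers open, and state the following for all remaining visits:

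- The measures already scheduled in Table 2 are taken in both arms by the existing trained research assistants, with the same instruments and procedure: height, weight, body fat and waist at each visit; blood pressure and step test at 6 and 12 months only. No assessment is added.
- Where the visit includes a clinic encounter, the measures come before it.
- The assistant who measures did not notify that family of its allocation and has no view of the allocation field in REDCap.

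Reconcile the seated position for blood pressure in the trial measures text with the supine position in Table 2, so that one procedure applies to both arms.

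For visits already completed, report who measured and whether they knew the arm. If masking is not feasible, say why in the Randomization section.

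Cost: rostering of existing staff around clinic flow and a REDCap access setting; no new visits. Some unmasking will remain, because families may disclose and the 6-month visit is itself informative. The change comes late in enrolment, so procedures will differ between earlier and later visits, which is why the report on completed visits is needed.

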#### Biospecimen population

A cohort of subjects participating in the primary trial will be included in the biospecimen analysis. Stool and blood serum samples will be collected at baseline and after the 6-month clinic-community intervention. Baseline samples will be from: (1) 100 obese adolescents (12–18 year olds); (2) 50 lean adolescent age- and sex-matched controls (12–18 year olds); (3) 100 obese children (5–11 year olds); and (4) 50 lean age- and sex-matched control children (5–11 year olds). Children and adolescents with obesity will be recruited through the primary study procedures until target sample size is met. Lean children will be recruited at the time of their well child visit, from the primary care clinic co-located with Healthy Lifestyles. Follow-up samples will only be collected from obese individuals.

We will build upon and expand resources that already exist within Duke University, namely, a biorepository of stool and blood serum samples from participants with obesity, aged 12–18, which has been established by a NIDDK-funded R24 grant (R24-DK110492). Analyses for Objective 2 will be conducted on samples from the expanded, shared biorepository. Figure 2 outlines patient samples that will come from the R24 cohort, and those that will come from this project.

**Fig. 2 Fig2:**
[figure not shown]
Overview of expansion of R24 Cohort by the newly funded Duke Center for Pediatric Obesity Research (American Heart Association Strategically Focused Research Network). Outline of which samples come from which cohort and age-group. Obese/lean is also listed. Only obese individuals will have follow-up samples collected

### Intervention

Subjects randomized to the intervention group enroll in the clinic-community intervention for 6 months. This includes Healthy Lifestyles clinic visits at baseline, 3-months, and 6-months, and twice-weekly sessions at the community center as described above. The clinic visits will include 30-min medical, dietary, and physical activity evaluation and counseling sessions. The sessions at the community center involve 30 min of warm up/check in time, at least 60 min of moderate-to-vigorous physical activity and 30 min of nutrition education. In total, subjects who participate fully will receive 4.5 h of clinical counseling, 52 h of physical activity, and 26 h of group-based nutrition counseling (108.5 h). In order to meet the recommended ≥26 h of contact over a 6-month period, subjects will need to participate in at least 25% of offered activities [5]. To enhance engagement and reinforce teaching, thrice-weekly text messages are sent to parent and child (if aged 11 or older, with parental permission) for the 6 months of the intervention. Within the community center, posters display playful characters designed to educate families about the experience and purpose of particular bodily sensations (e.g., Harold the Hunger Pain, Betty the Butterfly). These characters are further reinforced via text messages in which characters are reiterated, further information about that bodily sensation is provided, and information provided to increase interest in a variety of foods. Finally, monthly cartoon videos are designed to provide entertaining and accessible ways to put complex constructs like emotional eating and parent responsiveness into action.

The comparison group is an enhanced, 6-month wait list group. During the wait time, subjects will receive a non-obesity-related literacy intervention. This control intervention is consistent with Good Clinical Practice for the target population, as low-income families have fewer age-appropriate books per child in the home, and educational success is strongly mediated by literary skills [41, 42]. We will provide a $15 gift card each month to a locally owned book store in Durham. At the end of the 6-month wait time, subjects will be invited to participate in the intervention group.

### Measurement strategy

#### Trial measures

##### Body mass index:

The primary study outcome is BMI obtained through standardized measures of body weight and height using a digital scale and stadiometer [43]. Measures will be obtained at all data points. A large number of children referred to the healthy lifestyles clinic have a BMI significantly greater than the 95th percentile, and known challenges exist in measuring changes in BMI at extreme values. Therefore, as recommended by Flegal et al. we will assess and report child relative BMI, expressed as a standard deviation score (zBMI) and as a percent of the BMI value at the 95th percentile (%95th BMI) to evaluate and track obesity [44].

Cardiorespiratory Fitness is the principal secondary outcome, and will be assessed by heart rate at the completion of the YMCA submaximal bench-stepping test [45]. This was chosen over others due to its sensitivity to fitness-related changes in heart rate and ease of implementation in a mobile setting.

Given the complexity of pediatric obesity, a variety of secondary outcomes, including cardiovascular measures, social and emotional health, and behaviors, will also be assessed. Blood pressure will be measured with a calibrated auscultatory sphygmomanometer in the seated position with an appropriately sized cuff using standard methods [46]. Fasting blood sample for cardiometabolic biomarkers, including lipids, glucose, and transaminases will be obtained. Body fat percent will be measured using calibrated bioelectrical impedance. Parent BMI will be directly measured from parent height and weight using calibrated stadiometers.

Weight-specific quality of life will be measured using the validated “Sizing Me Up” child obesity-specific instrument, which has been used previously in the Healthy Lifestyles clinic population [47]. Research staff will administer survey-based instruments to the parent, child, or both to assess child temperament, mood, peer relationships, perceived family support, and body-esteem. We will employ measures developed by NIH PROMIS®, a patient-reported outcomes data management system to encourage more universal measurement of clinical outcomes across studies [48]. PROMIS is a data management system that allows researchers to choose independently validated items from domain-relevant item banks.

Child physical activity will be monitored by an activity tracker. Both intervention and control groups will receive activity trackers; recent evidence demonstrates that in the absence of coaching, an activity tracker alone does not impact body weight [49]. At the baseline visit, children will be provided with and taught how to use the activity tracker and to synchronize the data to the parent’s smartphone. Current guidelines recommend that children achieve 60 min of moderate-to-vigorous exercise, or 12,000 steps/day [50]. Subjects will wear the activity tracker continuously while in the study, and activity will automatically be collected, synced to the application by the participant, and downloaded daily by research assistants. The following data will be captured: steps/day and sleep. During participation in Bull City Fit, minutes/day of exercise and distance/day in miles will also be captured. We intentionally chose not to measure self-report dietary intake data because of the known poor internal and external validity of existing measures.

Multiple family characteristics are assessed as potential modifiers of intervention effectiveness, and to further characterize the population. Household income, transportation, parent stress, food insecurity, home food environment, and parental expectations for treatment will be collected by trained research staff at baseline using the instruments cited (Table 2). All parent measures will be available in English and Spanish.

**Table 2 Tab2:** Measures and Schedule of Assessments

Measure	Description	0 m	3 m	6 m	9 m	12 m
*Child and Family Characteristics*						
Demographic	Race and ethnicity, household income, transportation	x				
Child nutrition and activity habits; self-report (screener)	FLASHE Food and Activity Screeners, Teen Version (Ages 10+) [51]	x		x		x
Parent nutrition and activity habits; self-report (screener)	FLASHE Food and Activity Screeners, Parent version [51]	x		x		x
Other characteristics	Parent stress [52], food insecurity [53], home food environment [54], and parental expectations for treatment [55]	x				
*Primary Outcome*						
Child BMI	Directly measured height and weight using calibrated scales	x	x	x	x	x
Child body fat percent	Measured via bioelectrical impedance (Tanita, TBF 300, Arlington Heights, Ill).	x	x	x	x	x
Child Waist Circumference (cm)	Standardized waist circumference measured by trained personnel, using cloth measuring tape, at level of umbilicus	x	x	x	x	x
*Secondary Outcomes*						
Child fitness	Baseline, 3-min, 4-min and 5-min heart rate after submaximal (3-min) bench-stepping test (YMCA)	x		x		x
Child physical activity; objectively tracked	Garmin VivoFit 3; every week sync; day “counts” if > 10 h/d + 4/7 d/wk.	Continuous				
Child blood pressure	Measured with calibrated auscultatory sphygmomanometer, supine position, appropriately sized cuff [56].	x		x		x
Fasting lipid profile	Obtained as per standard protocol in Healthy Lifestyles clinic at enrollment	x		x		x
Fasting glucose	Obtained as per standard protocol in Healthy Lifestyles clinic at enrollment	x		x		x
Alanine aminotransferase	Obtained as per standard protocol in Healthy Lifestyles clinic at enrollment	x		x		x
Child QOL	Sizing Me Up/Sizing Them Up [47] (< 10 parent/child together, 10+ child complete but with parent nearby)	x		x		x
Depression	PROMIS databank	x		x		x
Anxiety	PROMIS databank	x		x		x
Loneliness	PROMIS databank	x		x		x
Friendship	PROMIS databank	x		x		x
Parent-child relationship	PROMIS databank	x		x		x
Body appreciation	Body appreciation scale (13-item)	x		x		x
Parent BMI	Directly measured height and weight using calibrated scales	x		x		x
Sleep duration/ quality	Garmin VivoFit 3	x	x	x	x	x
*Implementation Measures*						
Adoption	BPA usage and referrals	Continuous				
Engagement	Program log; number of hours of “contact” with intervention (clinic+community).	Continuous				
Fidelity	SOFIT	Continuous				
*Basic Science Measures*						
Research Blood	Fasting serum samples	x		x		
Stool microbiome	16S rRNA gene sequencing	x		x		

